## Abstract

**Background:**

Older patients with cancer experience cognitive impairment and a series of neurocognitive symptoms known as chemobrain due to chemotherapy. Moreover, older populations are disproportionately affected by chemobrain and heightened negative mental health outcomes after cytotoxic chemical drug therapy. Chinese acupuncture is an emerging therapeutic option for chemotherapy-induced cognitive impairment in older patients with cancer, despite limited supporting evidence.

**Objective:**

Our study aims to directly contribute to the existing knowledge of this novel Chinese medicine mode in older patients with cancer enrolled at the Department of Oncology/Chinese Medicine, Nanjing First Hospital, China, thereby establishing the basis for further research.

**Methods:**

This study involves a 2-arm, prospective, randomized, assessor-blinded clinical trial in older patients with cancer experiencing chemobrain-related stress and treated with Chinese acupuncture from September 30, 2023, to December 31, 2025. We will enroll 168 older patients with cancer with clinically confirmed chemobrain. These participants will be recruited through screening by oncologists for Chinese acupuncture therapy and evaluation. Electroacupuncture will be performed by a registered practitioner of Chinese medicine. The electroacupuncture intervention will take about 30 minutes every session (2 sessions per week over 8 weeks). For the experimental group, the acupuncture points are mainly on the head, limbs, and abdomen, with a total of 6 pairs of electrically charged needles on the head, while for the control group, the acupuncture points are mainly on the head and limbs, with only 1 pair of electrically charged needles on the head.

**Results:**

Eligible participants will be randomized to the control group or the experimental group in 1:1 ratio. The primary outcome of this intervention will be the scores of the Montreal Cognitive Assessment. The secondary outcomes, that is, attentional function and working memory will be determined by the Digit Span Test scores. The quality of life of the patients and multiple functional assessments will also be evaluated. These outcomes will be measured at 2, 4, 6, and 8 weeks after the randomization.

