Emerging chemotherapy-induced cognitive impairments in older patients with cancer are likely to widen without proper early intervention tactics. In this protocol, we propose a 2-arm, prospective, randomized, assessor-blinded trial to examine the efficacy and safety of EA for chemobrain among older patients with cancer who are on or about to receive chemotherapy. The aim of this study directly contributes to the existing knowledge in this area, thereby establishing a basis for further research. Changes in the scores on MoCA [17] and the incidence of adverse events serve as the primary outcome. Scores on the Digit Span Test will be the secondary outcome for attentional function and working memory [18]. The QoL and multiple functional assessments will also be evaluated [19]. Outcomes include the MoCA, Digit Span Test, QoL, and multiple functional assessments at 2, 4, 6, and 8 weeks after randomization. Data from this efficacy trial will determine whether Chinese EA successfully improves the symptoms of chemobrain and whether these improvements could markedly reduce the various side effects caused by cytotoxic chemotherapy drugs. If successful, findings from this study might have beneﬁts in reducing chemotherapy-induced working memory impairment. Data from this study may be used to support an implementation and dissemination trial of Chinese EA within real-world behavioral health and social service settings.

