### Specific Aims and Hypotheses

Chinese acupuncture is an emerging therapeutic option for chemotherapy-induced cognitive impairment in older patients with cancer, despite limited supporting evidence [23]. This study has 2 specific aims.

First, to evaluate the clinical therapeutic response of EA intervention for the treatment of chemobrain in older patients with cancer, a randomized controlled trial is designed to study the effects of EA on chemobrain at baseline, 2, 4, 6, and 8 weeks follow-up. We hypothesize that those assigned to EA will show greater reductions from baseline to follow-ups in MoCA Overall Anxiety Severity and Impairment Scale and Digit Span Test scores and greater reductions in cognitive impairment in daily responsibilities relative to the control group. We also hypothesize that the effectiveness of EA on QoL and multiple functional assessments will be similar across experimental or control groups.Second, our aim is to elucidate the modern biomedical mechanism of EA in the treatment of chemobrain in older patients with cancer. In testing the putative mechanisms of action, we hypothesize that the intervention effects on study outcomes will be mediated by reductions in chemotherapy-induced working memory impairment and the incidence of certain digestive, neurological, and distress-related symptoms.

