### Assessments

In this study, therapeutic efficiency will be assessed in terms of the following aspects: cognitive performance, fatigue, QoL, and chemotherapy-induced side effects. The primary outcome of this study is to verify whether EA is therapeutically useful for preventing chemobrain and alleviating the related symptoms and the safety of intervention. Cognitive performance will be assessed using MoCA + FACT-Cog. The secondary outcomes are as follows: QoL will be measured using EORTC QLQ-C30, fatigue will be assessed using the FACIT-Fatigue scale, and the manifestation of chemotherapy-induced side effects will be assessed using the Chemotherapy Symptom Rating Scale FAACT + FACT-BRM. All assessment scales will be evaluated by previously trained researchers at the following timepoints (see Figure 2): baseline (T0), midpoint of main treatment (T1-T3) once every 2 weeks, and end of the 8-week main treatment (T4) (a total of 5 timepoints). We will also keep a record of all the shedding cases. This study is a multidisciplinary clinical trial (across oncology and Chinese medicine disciplines) on the role of Chinese acupuncture as therapy for chemotherapy-induced cognitive impairment in older patients with cancer. If successful, findings from this study might have beneﬁts in reducing chemotherapy-induced working memory impairment. Data from this study may be used to support an implementation and dissemination trial of Chinese EA in real-world behavioral health and social service settings.

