### Statistical Analyses

Cognitive impairment is defined as those with SD>1.5 in the mean scores of MoCA and the QLQ-C30 at baseline for all participants at different timepoints. A time-series test in the Kaplan-Meier survival analysis will be used to compare the incidence of cognitive deficits accumulated after 8 weeks of acupuncture intervention between the 2 groups. Linear mixed-effects modeling will be used to compare participants’ cognitive impairment, fatigue, and depression at baseline, during, and after acupuncture intervention, where only those who have completed at least one assessment at baseline and during treatment will be compared. This model will use time and group as categorical fixed factors and random intercepts and use random intercepts in conjunction with a measurement covariance matrix. Participants’ age, chemotherapeutic drug dosage, fatigue at baseline, depression, and additional treatments will be considered as covariates in the statistical analyses. A 2-sided *t* test will be used to compare the covariates at each timepoint between the 2 groups. The chi-square test will be used for qualitative information and the *t* test will be used for continuous information at baseline. Statistical significance will be considered at *P*<.05. The study data used will be statistically analyzed using SPSS software (IBM Corp) under the supervision of a statistician. To ensure the privacy of the patients, all relevant study data and personal data will be kept in a locked file cabinet. Electronic data will be stored on an encrypted computer and will not be stored on any external storage device. Each participant will be assigned his or her own ID in the study record, which will be used in lieu of his or her name and personal identifying information. Clinical data from the study will be kept in a separate file from the participant’s personal data. The principal investigator will be responsible for all the clinical trial data. During and after the clinical trial, the principal investigator, researchers, and the ethical review committee have the right to view the study data. Participants will have the right to access their personal data and the results of the study. All study data will be stored for a minimum of 3 years after the completion of the trial, after which they will be destroyed in accordance with the rules of the ethics review committee.

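### The primary outcome is defined in three different, overlapping ways, and the sample size is built on a further quantity that is never labelled primary

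*Protocol article*

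**What the plan says.** Three places use the term primary outcome, and they differ.

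- Abstract, Results: "The primary outcome of this intervention will be the scores of the Montreal Cognitive Assessment".
- Introduction: "Changes in the scores on MoCA [17] and the incidence of adverse events serve as the primary outcome".
- Assessments: "The primary outcome of this study is to verify whether EA is therapeutically useful for preventing chemobrain and alleviating the related symptoms", with the safety of the intervention added. The next sentence gives the instruments: "Cognitive performance will be assessed using MoCA + FACT-Cog". FACT-Cog does not appear in the list of secondary outcomes that follows.

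Sample Size Estimation uses the incidence of chemobrain: 30% after chemotherapy, reduced by 10%-20% with acupuncture. Statistical Analyses opens with a case definition built on MoCA and the QLQ-C30, and then says: "A time-series test in the Kaplan-Meier survival analysis will be used to compare the incidence of cognitive deficits accumulated after 8 weeks". A linear mixed model for cognitive impairment, fatigue and depression comes after that. The only significance threshold is P<.05.

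The secondary outcomes also vary. The Abstract and Introduction name the Digit Span Test. The Assessments section lists quality of life, fatigue and side effects, without Digit Span.

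The first aim predicts "greater reductions from baseline to follow-ups in MoCA Overall Anxiety Severity and Impairment Scale and Digit Span Test scores", and also that "the effectiveness of EA on QoL and multiple functional assessments will be similar across experimental or control groups". The Abstract's Conclusions ask whether electroacupuncture can improve quality of life.

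**The concern.** A reader cannot tell from the article which result would make the trial positive. A mean MoCA score, a self-reported cognition score, a cumulative incidence and an adverse-event rate need different tests and answer different questions. The incidence case definition also draws on the QLQ-C30, which the Assessments section treats as secondary.

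Two things are at stake. First, the sample size was argued for incidence, so nothing in the article says what MoCA difference the trial can detect, although MoCA is in every labelled version of the primary. Second, with one undivided threshold and several candidates, the text leaves room to present whichever cognitive result is significant as the primary one.

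**Working it through.** **1. The statements side by side**

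| Place | Quantity | Called primary? |
|---|---|---|
| Abstract, Results | MoCA scores | yes |
| Introduction | MoCA change; adverse-event incidence | yes |
| Assessments | Prevention and relief of chemobrain (MoCA, FACT-Cog); safety | yes |
| Sample Size Estimation | Incidence of chemobrain | no |
| Statistical Analyses, first-named analysis | Cumulative incidence of cognitive deficits | no |

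MoCA is common to the first three rows. The wording on prevention in the third row points towards incidence but does not name it as an endpoint.

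**2. What enters the sample size**

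The inputs in Sample Size Estimation are p1 = 0.30, a reduction of 10%-20%, multiplier 10.5, a two-sided test, 80% power, 20% dropout and 84 per arm. Read as percentage points, p2 is 0.20 or 0.10.

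- Formula as printed, denominator not squared: (0.21 + 0.16)/0.10 × 10.5 = 38.9, so 39, or 49 after dropout. For p2 = 0.10: (0.21 + 0.09)/0.20 × 10.5 = 15.8, so 16, or 20 after dropout.
- Denominator squared: 0.37/0.01 × 10.5 = 388.5, so 389, or 486 after dropout. For p2 = 0.10: 0.30/0.04 × 10.5 = 78.75, so 79, or 99 after dropout.
- Standard pooled formula at the stated two-sided 5% and 80% power: 294 or 62, which is 368 or 78 after dropout.

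None of these gives 84. The printed formula comes near it (86, or 83 if dropout is added as n × 1.2) only if the reduction is read as 20% relative, and then only because the denominator is not squared. That is a separate matter, and this point does not depend on it. What matters here is that every reading uses two proportions. No mean, standard deviation or difference for MoCA or FACT-Cog enters, and no adverse-event rate.

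**3. False-positive risk if several candidates are each tested at two-sided 5%**

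For k independent tests the chance of at least one false positive is 1 − 0.95^k: 9.75% for k = 2 and 14.3% for k = 3. For correlated tests the figures come from simulating two-sided z tests with a common correlation r. The values of r are assumptions; the article gives none.

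| Tests | r = 0 | r = 0.5 | r = 0.7 | r = 0.9 |
|---|---|---|---|---|
| 2 | 9.7% | 9.1% | 8.4% | 7.0% |
| 3 (MoCA, FACT-Cog, incidence) | 14.3% | 12.5% | 10.9% | 8.4% |

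**4. What 84 per arm delivers for each choice of primary**

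After 20% dropout, 84 × 0.8 = 67 are evaluable per arm.

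- MoCA mean difference: d = (1.96 + 0.84) × √(2/n). For n = 67 this is 0.48 (0.49 with the t distribution); for n = 84 with no dropout it is 0.43. Any gain from baseline adjustment is not counted.
- Incidence, 67 per arm, two-sided 5%: power is 83% for 30% vs 10%, 55% for 30% vs 15% and 27% for 30% vs 20%.

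**The case against.** The strongest reply is that the versions overlap and that the rest is detail for an analysis plan. Several parts of that reply stand.

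- A reader might count four incompatible primaries. Only three statements carry the label, and all three include MoCA. Incidence is primary only by inference from the sample size and the order of the analyses.
- A reader might infer that the outcome is tested separately at weeks 2, 4, 6 and 8. The article does not plan this. It plans one incidence comparison over 8 weeks and one mixed model; the only t test at each timepoint concerns covariates.
- A reader might calculate inflation for four primary tests, 16-19% at correlations of 0.5 to 0. That counts adverse events as an efficacy test, and a chance safety difference is not a false claim of efficacy. It also assumes low correlation, although incidence is defined partly from MoCA, so those two share data.
- A multiplicity rule may exist in an analysis plan that is not shown. The inflation is therefore something the text permits, not something it prescribes.
- The secondary lists are not disjoint: the Abstract and Introduction also mention quality of life and functional assessments.
- The hypothesis wording is garbled rather than substantive. A reduction fits the anxiety scale named in the same phrase, the sentence goes on to predict less cognitive impairment, and two-sided tests are unaffected.

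What does not stand is the defence that this is omitted detail. The differing definitions are printed in the article, and an analysis plan that settled on one would still contradict the others.

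**Conclusion.** The point holds in this form: three overlapping but different definitions of the primary outcome, and a sample size and first-named analysis resting on a binary incidence that is never labelled primary. The success criterion is therefore undetermined in the article, and 84 per arm has no stated relation to the MoCA outcome.

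The false-positive risk the text permits is about 7-10% for two cognitive candidates and 8-14% for three, against a nominal 5%. This assumes that each is tested at two-sided 5%, with correlation between 0.9 and 0, and that no rule elsewhere limits it. Larger figures, based on four primaries or on separate tests at four visits, are not supported by the document.

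This should be corrected before outcome data are seen. The hypothesis wording in Specific Aims is a minor correction alongside it.

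**What to change.** 1. Declare one primary outcome. A natural choice is the between-arm difference in MoCA score at week 8 (T4), adjusted for baseline, from the planned mixed model, because MoCA is common to all three labelled versions. Name MoCA as the model's outcome and specify the week-8 group contrast.
2. Make FACT-Cog and incidence of impairment secondary outcomes in a stated order, and report adverse events as safety.
3. Align the Abstract, Introduction, Assessments, Sample Size Estimation and Statistical Analyses, including one secondary list that settles the place of Digit Span.
4. Restate the sample-size basis for the chosen primary. For MoCA, 84 per arm with about 67 evaluable detects a standardised difference of about 0.48-0.49 with 80% power at two-sided 5%; the sponsor must say why a difference of that size is plausible and worthwhile. If incidence is preferred as primary, it must be labelled so and its power restated.
5. In Specific Aims, predict greater improvement rather than reduction in MoCA and Digit Span scores (taking higher scores as better), and reconcile the hypothesis of similar quality of life with the Abstract's aim of improving it.

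No extra participants or visits follow from the relabelling itself. The sponsor gives up the choice among primaries and takes on the task of justifying n on a MoCA effect. With 11 of 168 participants recruited by October 21, 2023, the change was cheap at that date.

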**Conclusions:**

This efficacy trial will explore whether Chinese electroacupuncture can prevent chemobrain, alleviate the related symptoms, and improve the quality of life of older patients with cancer who are undergoing or are just going to begin chemotherapy. The safety of this electroacupuncture intervention for such patients will also be evaluated. Data from this study will be used to promote electroacupuncture application in patients undergoing chemotherapy and support the design of further real-world studies.

**Trial Registration:**

ClinicalTrials.gov NCT05876988; https://clinicaltrials.gov/ct2/show/NCT05876988

**International Registered Report Identifier (IRRID):**

DERR1-10.2196/53853

## Introduction

With the development of new cytotoxic drugs for clinical practice, the clinical curative effects and survival rates of patients with cancer have improved greatly [1]. However, these drugs have considerable adverse side effects that are pernicious, unexpected, and occur at standard doses when administered to older patients with cancer [2]. Studies have shown that older patients with cancer undergoing chemotherapy develop chemotherapy-induced cognitive impairment, known as chemobrain, including a series of neurocognitive symptoms (forgetfulness, trouble concentrating and remembering details, difficulty with multitasking word finding, and taking longer to finish tasks), hospitalizations, and poor quality of life (QoL) [3,4]. In fact, chemobrain-related stress has been reported disproportionately among older individuals with cancer who have undergone chemotherapy [5].

With advances in cancer treatment over the decades, the survival time of older patients with cancer has been gradually extended, and the accompanying symptoms of chemobrain have gradually drawn increasing attention [5]. Recent data have shown that chemobrain-related stress could persist for a long-term period after a systemic therapy, which is particularly relevant to older patients with cancer [6]. These individuals report chemobrain symptoms of anxiety and depressive disorder, and the number of older patients with cancer will increase dramatically in the coming future. Although data on cognitive impairment onset after chemotherapy are lacking for older patients with cancer in China, clinical practitioners have paid constant attention to the health of their constituents, given their propensity for worse physical and mental health outcomes related to chemotherapy [7]. Data suggest that up to two-thirds of older patients with cancer develop chemobrain during or after chemotherapy [8]. Most of these patients experience cognitive impairments for months, but 10%-20% of these individuals experience persistent chemobrain-related stress even after many years of completing chemotherapy. In recent years, the incidence rate of cancer in senile patients has been rising in China [9]. The problem of chemotherapy-induced cognitive dysfunction is becoming increasingly common, and there are growing concerns that chemobrain could become a threat. Therefore, it is crucial to explore an intervention that can effectively prevent and treat chemotherapy-induced cognitive impairment in older patients with tumors.

Pre-existing studies [10] have shown that some neuroprotective factors such as methylphenidate and modafinil are effective for treating chemotherapy-related cognitive impairment; however, most clinical trials on interventions for chemobrain report less access to control groups and less treatment engagement. Combo acupoint stimulation therapy is a new technique based on the theory of traditional Chinese medicine and modern biological principles. With the help of invasive or noninvasive interventions, different stimuli or drug intakes would be administered at acupuncture points, meridians, or related specific body surface sites [11].

Acupuncture has been used for thousands of years in China and other Asian countries to treat various diseases, including sleep disturbance [12]. It is a nonpharmacological therapy that involves inserting needles into acupuncture points and sometimes applying minielectrical current stimulation on acupuncture points via needles or applying acupressure on the surface of points in different parts of the body, including ear and scalp [12]. Electroacupuncture (EA) is an effective family member of combo acupoint stimulation [13]. Lyu et al [14] reported that EA could be effective in alleviating various side effects caused by anticancer drugs, such as pain, vomiting, fever, fatigue, dry mouth, anxiety, depression, and insomnia. In addition, EA could promote the rehabilitation of pathological microstructures in the brain and improve the cognitive ability of patients with cognitive impairment. Clinical trials [14,15] of acupuncture for preventing and managing mild cognitive impairment in older adults show that it can improve the clinical efficacy rate, Mini-Mental State Examination Scale score, Montreal Cognitive Assessment (MoCA) test score, and clock drawing task scores, suggesting that acupuncture can be an effective approach complementary to existing therapies. Evidences [14] from acupuncture in patients after an ischemic stroke support its role in the treatment of neurological deficits through modulation of neuroplasticity. Chemobrain affects cognitive function, in particular, think and memory functions through various mechanisms, including inflammation and oxidative stress, which may lead to neurogenesis and glycogenesis reduction. This pathological process shares some similarities with brain damage after an ischemic stroke [3,16]. Therefore, it is important to investigate if EA is effective in preventing and treating chemobrain in older patients with cancer and for improving the QoL of cancer survivors.

Emerging chemotherapy-induced cognitive impairments in older patients with cancer are likely to widen without proper early intervention tactics. In this protocol, we propose a 2-arm, prospective, randomized, assessor-blinded trial to examine the efficacy and safety of EA for chemobrain among older patients with cancer who are on or about to receive chemotherapy. The aim of this study directly contributes to the existing knowledge in this area, thereby establishing a basis for further research. Changes in the scores on MoCA [17] and the incidence of adverse events serve as the primary outcome. Scores on the Digit Span Test will be the secondary outcome for attentional function and working memory [18]. The QoL and multiple functional assessments will also be evaluated [19]. Outcomes include the MoCA, Digit Span Test, QoL, and multiple functional assessments at 2, 4, 6, and 8 weeks after randomization. Data from this efficacy trial will determine whether Chinese EA successfully improves the symptoms of chemobrain and whether these improvements could markedly reduce the various side effects caused by cytotoxic chemotherapy drugs. If successful, findings from this study might have beneﬁts in reducing chemotherapy-induced working memory impairment. Data from this study may be used to support an implementation and dissemination trial of Chinese EA within real-world behavioral health and social service settings.

